### Statistical analyses

To test normality of continuous data, the Shapiro-Wilk test will be used. Continuous data will be presented descriptively with means and SDs. When continuous data are not normally distributed, the median and inter quartile range (IQR) will be presented. For ordinal data, both the median and IQR will be presented. Nominal data will be presented as numbers and percentages. Comparison between normally distributed groups will be done with the independent t-test when data are normally distributed. For non-normally distributed data, the Mann-Whitney U test will be used. Nominal data will be compared by the Chi-square test or Fisher-exact test when a particular cell is < 5. For all different groups, statistical analyses will be performed for intention-to-treat (ITT) and instrumental variable analysis [47]. An interim analysis will be conducted after 26 patients underwent the PEI to evaluate the power calculation. The incremental cost-effectiveness ratio (ICER) will be calculated as the difference in costs divided by the difference in QALYs between groups. When data are missing, ‘available case analyses’ will be used, indicating that missing cases will be discarded in the variables that are needed for a specific analysis. All analyses will be performed using statistical package for the social sciences (SPSS). A *p*-value below 0.05 is considered statistically significant.

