### Sample size

The sample size calculation is based on the primary outcome, the 6MWT. The power of the study is set on 80% (ß), using differences between two independent means with a 0.05 two-sided significance level. For calculation of the sample size, G*Power 3.1.9.2. was used [31]. Means and standard deviations (SDs) of the 6MWT of the study of Samuel et al. [19] were used. The first mean (SD) [483.16 (88.24)] is of patients with HNC who received the exercise intervention during (C/B)RT and the second mean (SD) [374.52 (110.26)] is of patients with HNC who received usual exercise care during (C/B)RT. Based on this, an effect size of 1.09 was calculated, which resulted in a sample size of 15 patients needed to undergo the PEI. We expect a drop-out of 24% as stated in the study of Samuel et al. [19]. Therefore, 20 patients need to be included in the PEI group. A feasibility study for PEI for patients with HNC in a Dutch population showed that 36% of the approached patients signed IC [13]. To include enough patients, a bigger sample size is needed. Using the expected participation percentage of 36%, a sample size of 56 is needed for the PEI group. Randomisation will be done in a 1:1 ratio so also 56 patients are needed in the control group. In total, 112 patients are needed. With the TwiCs design, two subgroups will arise in the PEI group, consisting of patients who accept and patients who refuse to undergo the PEI [26]. This type of non-compliance (refusal of the assigned treatment) will not be identical between the study arms [32]. Therefore, the sample size calculation will be revised when the real acceptance rate of the PEI differs from the initially estimated acceptance rate, before the end of the study [33].

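### The interim trigger of 26 PEI patients does not fit a plan that expects about 20: the look either seldom happens or comes after the planned 112 are randomised

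*Protocol article*

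**What the plan says.** Three sections of the protocol article bear on this.

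- **Sample size** derives 15 patients for the PEI and, after drop-out, concludes that "20 patients need to be included in the PEI group". Dividing by an expected 36% participation gives 56 to be invited, and 1:1 allocation gives 112 in total. The section adds that "the sample size calculation will be revised when the real acceptance rate of the PEI differs from the initially estimated acceptance rate", at some time before the study ends. It names no count or date for this.
- **Randomisation and blinding** provides a box of 112 envelopes, 56 with an invitation and 56 without. The same paragraph says the study goes on until 56 patients have accepted the PEI.
- **Statistical analyses** sets the only scheduled look: "An interim analysis will be conducted after 26 patients underwent the PEI to evaluate the power calculation". It does not say which quantity is examined. The final criterion is a p-"value below 0.05 is considered statistically significant", with no adjustment mentioned.

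**The concern.** The look is timed by the number of patients treated, and that number depends on the acceptance rate, one of the assumptions in the calculation under review. The trigger is also 30% above the number of PEI patients the plan expects by its end (26/20 = 1.30). Counting treated patients makes the look likely when acceptance is high and unlikely when it is low.

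Low acceptance is the case that matters for power. As an illustration, assume the planned effect (d = 1.09) in acceptors and none in refusers. The intention-to-treat effect is then d × acceptance. With 56 per arm and no drop-out, power is 81% at 50% acceptance, 54% at 36%, 40% at 30% and 30% at 25%.

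The content of the look is also open. The power calculation is built from two arm means and SDs, so a look that evaluates it could be read as including the between-arm 6MWT difference, while the final test stays at 0.05.

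**Working it through.** **Inputs.** From Sample size: means (SDs) 483.16 (88.24) and 374.52 (110.26), two-sided 0.05, 80% power, 24% drop-out, 36% acceptance, 1:1 allocation. From Randomisation and blinding: 56 invitation envelopes of 112, and the 56-acceptor rule. From Statistical analyses: trigger 26.

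**1. The plan's own figures reproduce.**
- Pooled SD = √((88.24² + 110.26²)/2) = 99.86, so d = (483.16 − 374.52)/99.86 = 1.09.
- Two-sample t-test power is 0.791 at 14 per group and 0.820 at 15, so 15.
- 15/(1 − 0.24) = 19.7, so 20. Then 20/0.36 = 55.6, so 56, and 2 × 56 = 112.

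**2. If recruitment ends with the 56 invitations.** Acceptors follow a Binomial(56, p) distribution. The expected number at p = 0.36 is 56 × 0.36 = 20.2. For 26 to be the expected number, acceptance must be 26/56 = 46%.

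**3. If recruitment runs to 56 acceptors.** The trigger is always met. The expected number invited by then is 26/p, and the number randomised is twice that.

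| Acceptance p | Step 2: P(at least 26 of 56) | Step 3: invited at trigger | Step 3: randomised at trigger |
|---|---|---|---|
| 25% | 0.04% | 104 | 208 |
| 30% | 0.7% | 87 | 173 |
| 36% | 7.0% | 72 | 144 |
| 40% | 20% | 65 | 130 |
| 50% | 75% | 52 | 104 |

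If having undergone the PEI means completing it, p in step 2 becomes 0.36 × 0.76 = 0.274 and the probability at the planned acceptance falls to about 0.2%.

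**4. Type I error, by assumed use of the look.** These figures come from simulation under no effect (z-test, 400,000 runs).
- Acceptance rate or SD pooled over arms only: essentially unchanged at 5%.
- Interim effect used to re-size the trial, final test at 0.05, look at 46% of planned N, cap 1.5 to 3 times planned N: about 5.6% to 6.3% if N can only rise, about 6.6% to 7.2% if it can also fall.
- Efficacy tested at 0.05 at a half-way look and again at the end: about 8.3%.

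**The case against.** The best defence is the 56-acceptor rule. Under it 26 is 46% of the target (26/56), which is an ordinary near-half-way look, and the abstract and the Participants section describe the cohort as at least 112, a floor and not a cap. This stands as far as it goes: one cannot say flatly that the interim will not happen. But 56 acceptors at 36% acceptance means 56/0.36 = 156 invited and about 311 randomised, a total that appears nowhere in the article and that the 112 envelopes cannot supply. Measured against the stated 112, the look still comes too late.

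A reader might infer that this interim is the trial's only protection against low acceptance. The article does not support that. The acceptance-based revision in the Sample size section is not tied to the 26-patient look. Acceptance is known soon after invitation and refusers are listed, so the revision could be made at any time.

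A reader might also infer that the type I error is already above 5%. That is not supported either. The article states no interim efficacy test, no early stopping and no use of the interim effect. The 8.3% belongs to a design it does not propose. It does not say who carries out the look, and the quantity examined may be defined in a full protocol or analysis plan that is not shown.

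**Conclusion.** The point holds as a mismatch between stated figures. The numbers 20 (expected PEI patients), 26 (trigger) and 56 (invited in one place, acceptors in another) cannot all belong to one plan.

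- If the 112-envelope plan governs, the look has a 7% chance of occurring when every planning assumption is true, and under 1% at 30% acceptance or below.
- If the 56-acceptor rule governs, the look is certain, but at the planned acceptance or lower it falls after at least about 144 randomisations.

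These results assume independent acceptance decisions at a constant rate. They also count a patient as having undergone the PEI once the invitation is accepted, and a stricter definition makes the first case worse. The timing fault does not depend on any unseen document. The type I error issue is an ambiguity in wording, to be closed in the same edit, and is not a demonstrated error.

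**What to change.** 1. Reconcile the 20, 26 and 56 across Sample size, Randomisation and blinding, and Statistical analyses. State one recruitment stopping rule, and say how further envelopes are prepared if the total exceeds 112.
2. Time the look by number randomised or invited, for example after 56 randomised (about 28 invited, 28 × 0.36 = about 10 acceptors expected). This works under either stopping rule and at any acceptance rate.
3. Limit the look to the acceptance rate, drop-out and the 6MWT SD pooled over arms. State that no between-arm comparison is made, so the final 0.05 threshold needs no adjustment.
4. Say that this look is, or is not, the occasion for the acceptance-based revision promised under Sample size.

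The cost is protocol wording, to be settled before any look is taken. The interim would give no information on effect size. With 28 invited the acceptance estimate is also rough: its standard error at 36% is √(0.36 × 0.64/28) = 9 percentage points. Because no arms are compared, the acceptance count can be repeated later at no cost in type I error.

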### Measurements

The socio-demographic data (age, gender, education, employment and marital status) and medical data (tumour site, disease stage, comorbidity, HPV status, tobacco and alcohol use, nutrition status and type of treatment) will be assessed at baseline (M0). Physical performance, muscle strength, fatigue, QoL, BMI, nutritional status, and physical activity will be assessed at baseline (M0), 12 weeks (M1) and 6 (M2) and 12 (M3) months after baseline. Treatment tolerability will be assessed at M1, M2 and M3. Health related costs will be collected at M3. All tests and Dutch questionnaires are validated and have satisfying clinimetric properties.

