(C/B)RT tolerability will be retrieved from medical records and registered as the percentage of scheduled treatment completion, percentage of (C/B)RT adjustment and type of (C/B)RT adjustment. Furthermore, toxicity will be registered from medical records, which includes the presence of pain, mucositis, dysphagia, aspiration, nausea and vomiting, and dry mouth according to the common terminology criteria for adverse events v 4.0 (CTCAE). To assess health related costs, a cost-effectiveness analysis will be performed for one year. Treatment data will be retrieved from medical records. Price levels of the years during this study will be used. By using the EQ-5D-5L and health related costs, the quality-adjusted life years (QALYs) can be calculated.

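### The ICER denominator is described as a plain between-group QALY difference; adjusting it for the EQ-5D-5L utility already collected at M0 would make it more precise at almost no cost

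*Protocol article*

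**What the plan says.** The protocol article, Statistical analyses, defines the economic result: "The incremental cost-effectiveness ratio (ICER) will be calculated as the difference in costs divided by the difference in QALYs between groups". For continuous data the same section names the t-test, "Comparison between normally distributed groups will be done with the independent t-test when data are normally distributed", with the Mann-Whitney U test as the alternative. It adds that "statistical analyses will be performed for intention-to-treat (ITT) and instrumental variable analysis [47". It names no covariate model and no use of a baseline value.

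Secondary outcomes lists the EQ-5D-5L among the QoL questionnaires, states that "a cost-effectiveness analysis will be performed for one year", and says of the QALY only this: "By using the EQ-5D-5L and health related costs, the quality-adjusted life years (QALYs) can be calculated". Measurements says that QoL and the other repeated outcomes "will be assessed at baseline (M0), 12 weeks (M1) and 6 (M2) and 12 (M3) months after baseline". Randomisation and blinding places randomisation immediately after the M0 measurement. M0 utility is therefore a pre-randomisation value, planned for every patient.

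**The concern.** Utilities within a patient are correlated over time. A patient who starts with high utility tends to accumulate more QALYs over the year, whatever the group. If the QALY is an area under the utility curve, M0 is also its first point. Using M0 in that way does not correct an imbalance between the groups; it adds the imbalance to the difference.

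The true QALY difference by randomised group is likely to be small, because the Sample size section expects only 36% of invited patients to accept the exercise programme. A chance M0 imbalance of ordinary size could then be about as large as the effect. The Discussion presents cost-effectiveness as a main contribution of the trial, so the precision of this denominator matters. Adding baseline 6MWT to the primary analysis would not help, because the QALY does not pass through that model.

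**Working it through.** **Arm size (from the document).** The plan gives no figure for QALYs; its only relevant figure is 56 per arm, which reproduces.
- Effect size = (483.16 − 374.52)/√[(88.24² + 110.26²)/2] = 108.64/99.86 = 1.09.
- The noncentral t gives power 0.791 at 14 per group and 0.820 at 15, so 15.
- 15/0.76 = 19.7, so 20; 20/0.36 = 55.6, so 56 per arm.

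**Assumptions (not in the document).** One-year QALY as trapezoid area under the EQ-5D-5L utility curve; utility SD s = 0.20 (0.15 to 0.25); equal correlation r between visits of 0.5 (0.3 to 0.7); a gain of 0.05 QALY in patients who accept and none in those who refuse.

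**Weights.** Visits at 0, 12, 26 and 52 weeks give 6/52, 13/52, 20/52 and 13/52 = 0.115, 0.250, 0.385 and 0.250 (sum 1; sum of squares 0.286).

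**Variance and slope.**
- Var(QALY) = s²[(1 − r) × 0.286 + r]. At r = 0.5: 0.04 × 0.643 = 0.0257, so SD 0.160.
- Slope of QALY on M0 utility = 0.115 + 0.885r = 0.558 (0.38 to 0.74).
- R² = slope²/[(1 − r) × 0.286 + r] = 0.311/0.643 = 0.48 (0.29 at r = 0.3; 0.69 at r = 0.7).

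**Chance imbalance.** SE of the M0 utility difference = 0.20 × √(2/56) = 0.038. One SE of imbalance moves the QALY difference by 0.558 × 0.038 = 0.021 (0.011 to 0.035 over the ranges of s and r). Only 0.115 × 0.038 = 0.004 of this comes from M0 as the first point of the curve; the rest comes through correlation with later visits.

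**Diluted effect.** 0.36 × 0.05 = 0.018 QALY.

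**Precision.** Unadjusted SE = 0.160 × √(2/56) = 0.030. Adjusted SE = 0.0303 × √(1 − 0.48) = 0.022. Without adjustment, the same SE would need about 56/0.516 = 108 patients per arm.

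**Wrong-sign probability, Φ(−0.018/SE), s = 0.20:**

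| r | SE unadjusted | SE adjusted | Wrong sign unadjusted | Wrong sign adjusted |
|---|---|---|---|---|
| 0.3 | 0.027 | 0.023 | 25% | 21% |
| 0.5 | 0.030 | 0.022 | 28% | 20% |
| 0.7 | 0.034 | 0.019 | 30% | 17% |

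**Power** (r = 0.5, two-sided 0.05, normal approximation). It rises from 9% to 13% for a difference of 0.018, and from 22% to 38% for 0.036 (a gain of 0.10 in patients who accept).

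**Sensitivity.**
- If the 0.05 is a utility gain at the follow-up visits only, the diluted difference is 0.36 × 0.05 × 0.885 = 0.016 and the wrong-sign probability falls from 30% to 23%. Over the full ranges of s and r it is 21% to 35% unadjusted and 13% to 29% adjusted.
- With a utility gain of 0.10 (difference 0.032) it falls from 15% to 7%.
- With 42 per arm after 24% drop-out (56 × 0.76 = 42.6), the SE falls from 0.035 to 0.025.
- Randomisation and blinding also says that the study continues until 56 patients have accepted. At 36% acceptance that means 56/0.36 = 156 invited. With 156 per arm the SE falls from 0.018 to 0.013 and the wrong-sign probability for 0.018 from 16% to 8%.

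**The case against.** The strongest objection is that the ICER sentence is the standard definition. It does not say that the difference is unadjusted, and a regression coefficient for group is also a difference in QALYs between groups. The article gives no QALY algorithm, so it plainly condenses this part, and adjustment for baseline utility is often left to an analysis plan that is not shown here. This stands as a limit. A reader might infer that the plan discards M0 utility; the article does not say so, and an area-under-the-curve QALY would use M0 as its first point. What remains is that the article sets out its tests, ICER formula, missing-data rule and software together, and every comparison that it names for continuous data is unadjusted. The point is therefore a better method on data already held, rather than a complaint about missing detail.

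A second objection is that randomisation makes the unadjusted difference unbiased. That is correct. The gain is in precision, and in protection against whatever imbalance happens to occur.

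A third is that the size is assumed and that most of the wrong-sign risk stays after adjustment. Both are true: 20% of the central 28% remains, because the trial is small and the effect is diluted.

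**Conclusion.** The point holds as a low-cost improvement to a secondary analysis, and it is worth making. As described, the incremental QALY is a simple group difference beside unadjusted tests. Under the central assumptions, adjustment for M0 utility lowers its SE from about 0.030 to 0.022 (variance down 48%, range 29% to 69%) and the wrong-sign probability for a diluted difference of 0.018 from about 28% to 20%. The direction of the gain does not depend on the arm size: the SE falls at 42, 56 and 156 per arm. Its size depends on a utility SD, a correlation, a QALY gain and a QALY algorithm that the document does not give.

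A reader might go further and infer that an M0 imbalance could move the programme from dominant to dominated. The documents do not support that. The imbalance enters the denominator only, whereas moving from cheaper and better to dearer and worse needs the cost difference to change sign as well, and no costs are given. Nor is omission of M0 utility the only source of sign error, since ordinary sampling error remains after adjustment. The 6MWT sample size figures are not affected.

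**What to change.** In Statistical analyses, state that one-year QALYs are the area under the EQ-5D-5L utility curve over M0, M1, M2 and M3. State that the incremental QALY is the coefficient for randomised group from a linear regression of that QALY on group and M0 utility. Use this coefficient as the ICER denominator in the ITT analysis, and report the unadjusted difference as a sensitivity analysis. If an unpublished analysis plan already does this, one sentence would bring the article into line.

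The cost is a short addition to the text and one regression in SPSS. No extra data, visits or patients are needed. A patient with a complete area-under-the-curve QALY already has M0 utility, so the adjustment excludes nobody further. Fixing the model in advance also avoids a later choice between two available answers.

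### The article counts costs among the inputs to QALYs, and its general rules for skewed and missing data, with no exemption for costs or QALYs, do not fit the mean-based ICER it plans

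*Protocol article*

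**What the plan says.** Protocol article, Secondary outcomes: the economic evaluation covers a fixed horizon ("To assess health related costs, a cost-effectiveness analysis will be performed for one year"), with treatment data taken from medical records. The QALY is described in one sentence: "By using the EQ-5D-5L and health related costs, the quality-adjusted life years (QALYs) can be calculated".

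Protocol article, Statistical analyses: the economic estimate is "The incremental cost-effectiveness ratio (ICER) will be calculated as the difference in costs divided by the difference in QALYs between groups". The same section sets general rules for continuous data:

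- "To test normality of continuous data, the Shapiro-Wilk test will be used".
- "When continuous data are not normally distributed, the median and inter quartile range (IQR) will be presented".
- "For non-normally distributed data, the Mann-Whitney U test will be used".

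On missing data: "When data are missing, ‘available case analyses’ will be used, indicating that missing cases will be discarded in the variables that are needed for a" (the quote breaks off just before the sentence ends; its last words tie the rule to each analysis separately).

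None of these rules names costs or QALYs, and none exempts them. The section also commits to intention-to-treat and instrumental variable analyses. Under Measurements, quality of life (which includes the EQ-5D-5L) is assessed at M0, M1 (12 weeks), M2 (6 months) and M3 (12 months), and costs are collected at M3.

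**The concern.** A QALY is health-state utility accumulated over time. Costs do not enter it. The sentence in Secondary outcomes is the only account the article gives of how the ICER's denominator is obtained, and it lists the numerator as an input.

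An ICER needs the difference in arithmetic mean cost, because only the mean scales up to what a hospital or insurer pays in total. Healthcare costs are usually right-skewed and so would normally fail a normality test. The general rule would then summarise them by medians and test them by ranks. The published cost comparison and the ICER beside it would answer different questions and could disagree.

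A one-year QALY calculated per patient from four visits needs all four utilities. Discarding incomplete cases shrinks the sample. It also gives an unbiased comparison only if loss is unrelated to utility and cost, which is doubtful in patients under a treatment schedule the Discussion itself calls demanding. Because treatment data come from medical records, costs may be known for patients who returned no questionnaire. The rule then either throws away known costs or forms the numerator and denominator from different sets of patients.

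**Working it through.** **The plan's own figure.** The only computed design figure is the sample size for the 6MWT. Pooled SD = sqrt((88.24² + 110.26²)/2) = 99.86; d = (483.16 − 374.52)/99.86 = 1.09. A two-sample t-test at two-sided 0.05 and 80% power needs 14.29 per arm, rounded up to 15. 15/0.76 gives 20; 20/0.36 = 55.6 gives 56; doubled, 112. It reproduces, and nothing below changes it.

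**QALY sentence.** Set the two sections side by side. Secondary outcomes puts costs among the QALY inputs. Statistical analyses puts costs in the numerator and QALYs in the denominator. The second is right. If costs also entered the QALY, they would appear on both sides of the ratio.

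**Rank-test rule.** The article gives no cost figures, so this part rests on assumed log-normal costs with 56 per arm.

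- Would skewed costs reach the rank test? At log-SD 0.6, Shapiro-Wilk rejected normality in 98.8% of 1,000 simulated samples of 56. In practice, yes.
- Does the rank test address the mean? With equal medians and log-SDs s1 and s2, the ratio of mean costs is exp((s2² − s1²)/2). Over 4,000 simulated trials per row:

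| s1 v s2 | Ratio of mean costs | Mann-Whitney rejects | Welch t rejects |
|---|---|---|---|
| 0.6 v 1.0 | exp(0.32) = 1.38 | 4.6% | 27% |
| 0.8 v 1.1 | exp(0.285) = 1.33 | 4.9% | 15% |

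Mean costs differ by a third or more, yet the rank test rejects only at about its nominal 5%. The t-test's power is low too. The point is that the rank test does not look at the quantity the ICER uses.

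- How far apart are the summaries? For a log-normal variable, median/mean = 1/sqrt(1 + CV²). At CV 1 this is 1/sqrt(2) = 0.71.

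**Available-case rule.** Assume M0 is complete and each of M1 to M3 is missed independently with probability m. The fraction with a complete series is (1 − m)³.

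| m | Fraction complete | Of 112 |
|---|---|---|
| 5% | 0.857 | 96 |
| 10% | 0.729 | 82 |
| 15% | 0.614 | 69 |

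Independence matters. If the same patients missed every visit, m = 10% would leave 0.9 × 112 = 101. As another reference point, the 24% drop-out in the Sample size section, if extended to the whole cohort, would leave 0.76 × 112 = 85; the article applies that rate only to the PEI participants. The fractions do not depend on the total, so they hold if more than 112 patients are enrolled.

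**The case against.** The ICER sentence is the standard definition and contains no error. The QALY sentence is probably loose wording for the inputs to the whole economic evaluation, since the analysis section keeps costs and QALYs apart. The Mann-Whitney sentence is generic and does not name costs, and the one sentence specific to the economic comparison speaks of a difference in costs, not in medians. Available-case analysis could also mean averaging utility visit by visit over whoever attended. Costs are a secondary outcome, and every magnitude above rests on assumed inputs.

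Much of this stands. The ICER formula is untouched, and the QALY error is one sentence to edit. But costs are continuous data, comparing them is part of the stated aim, and no exemption is given, so an analyst following the text would apply the rank rule to them. Visit-by-visit averaging is a possible reading, but it still lets different patients contribute to different parts of the same QALY difference, and to the cost difference.

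A reader might infer stronger points that the article does not support:

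- *That the ICER will be reported without any uncertainty.* The article is silent on this. A condensed article may leave intervals, the cost-effectiveness plane and acceptability curves to a fuller plan that is not shown.
- *That patients who die are dropped.* Death is never mentioned. Nothing prevents assigning zero utility from death, and such a value need not count as missing.
- *That inflation distorts the comparison.* The wording "Price levels of the years during this study will be used" does not exclude later conversion to one price year, and 1:1 randomisation exposes both arms to the same years. This is reporting detail.
- *That the QALY difference would often have the wrong sign.* Any such probability rests wholly on an assumed QALY gain and SD, for which the article gives no figures.

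**Conclusion.** The point holds in limited form. The sentence deriving QALYs from costs is wrong as written, though probably a slip. The general rules, followed literally, would compare skewed costs on a quantity other than the mean difference in the ICER. They would also lose patients with incomplete EQ-5D-5L data from the one-year QALY, or mix patient sets between numerator and denominator. The first effect rests on costs being skewed enough to fail Shapiro-Wilk, the second on the natural reading of the available-case rule. The illustrated loss, from 112 to between 96 and 69 complete series, assumes 5% to 15% independent missingness per follow-up visit and is not a forecast. Neither the primary analysis nor the sample size is affected. A better method is available at low cost, so the text should be changed before the data are analysed.

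**What to change.** 1. Correct the sentence in Secondary outcomes: QALYs are the area under the EQ-5D-5L utility curve from M0 to M3, and costs enter only the ICER numerator.
2. In Statistical analyses, exempt costs and QALYs from the median/IQR and Mann-Whitney rule and from the available-case rule.
3. Compare arithmetic mean costs and arithmetic mean QALYs by randomised group, in line with the intention-to-treat commitment already made, with QALYs adjusted for M0 utility.
4. Use multiple imputation for missing utilities and costs, so that both differences come from the same patients, and give bootstrap intervals in place of the rank-test p-value.

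This takes a little more analysis work. It needs no new visit or questionnaire and no change to the sample size. If a fuller protocol or health-economic plan already says this, a cross-reference and the corrected QALY sentence are enough.

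### Available-case analysis with unadjusted two-group tests is the only stated handling of missing data; if drop-out differs between arms, it may bias the follow-up comparison in either direction.

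*Protocol article*

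**What the plan says.** The Statistical analyses section of the protocol article gives one rule for missing data, available-case analysis, "indicating that missing cases will be discarded in the variables that are needed for a specific analysis". The comparison it applies to is an unadjusted two-group test: "Comparison between normally distributed groups will be done with the independent t-test when data are normally distributed", with the Mann-Whitney U test otherwise. The same section says that "statistical analyses will be performed for intention-to-treat (ITT) and instrumental variable analysis".

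The Sample size section states "We expect a drop-out of 24" per cent, takes that figure from an earlier exercise trial, and uses it to raise the number undergoing the PEI from 15 to 20. It gives no drop-out figure for the control group.

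The Measurements section lists physical performance, strength, fatigue, QoL, BMI, nutritional status and physical activity as "will be assessed at baseline (M0), 12 weeks (M1) and 6 (M2) and 12 (M3) months after baseline". The article names no analysis that uses these visits jointly.

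**The concern.** Recruiting more patients to cover drop-out protects precision. It does not protect against selection. Three features of this trial make selection plausible.

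- **The outcome needs attendance and walking ability.** The Background describes loss of strength, fatigue and reduced physical performance as consequences of treatment. Patients who deteriorate may be the least likely to return for a walking test.
- **The arms may lose patients for different reasons.** Only one arm is invited to a programme of two supervised and three home sessions a week. That programme is meant to limit deterioration, and allocation is unblinded. The Discussion accepts that appointment burden can lead to refusal.
- **Each visit would be analysed on a different subset.** Discarding randomised patients visit by visit weakens the ITT label. It also makes the randomised group a less secure instrument for the instrumental-variable analysis.

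The economic analysis is exposed as well. Treatment data for costs come from medical records, while QALYs need the EQ-5D-5L questionnaires. Under a variable-by-variable rule, the cost difference and the QALY difference in the ICER could come from different patients.

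**Working it through.** **1. The plan's own figures reproduce.**
- Pooled SD = sqrt((88.24² + 110.26²)/2) = 99.86 m. Difference = 483.16 − 374.52 = 108.64 m. d = 108.64/99.86 = 1.09.
- Two-sided t-test at 0.05: power is 79.1% with 14 per group and 82.0% with 15, so 15.
- Drop-out: 15/0.76 = 19.7, so 20. Participation: 20/0.36 = 55.6, so 56. Two arms: 112.

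**2. How many patients the rule could discard.**
- If 24% applied to both arms: 112 × 0.24 = 26.9, about 27 patients, leaving 56 × 0.76 = 42.6, about 43 per arm.
- If it applied only to those who accept the PEI: 56 × 0.36 = 20.2 acceptors, and 20.2 × 0.24 = 4.8, about 5 patients.
- The article applies the figure in the second way and is silent on controls, so the true number is unknown.

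**3. Bias at a later visit, drop-out depending on the 12-week walk.** The inputs are assumptions, since the article gives no missingness mechanism: 56 per arm, SD 100 m, correlations between visits 0.7 to 0.8, true difference 40 m (close to the planning difference diluted by acceptance, 0.36 × 108.64 = 39.1 m), and drop-out odds about 2.7 times higher per 100 m shorter walk at 12 weeks.

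| Drop-out control / PEI | Bias of available-case t-test |
|---|---|
| 24% / 24% | about 0 m |
| 24% / 19% | about −4 m |
| 12% / 24% | about +8 m |

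The error favours the arm that loses more patients, because losing its weakest walkers raises its mean. An analysis using the baseline and 12-week walks brings the bias to about 0 m in each row.

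**4. Where the precision comes from.** Same setting, drop-out 24% control and 18% PEI, 12-week effect also 40 m:

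| Analysis | Mean estimate | SE |
|---|---|---|
| Available-case t-test | 36.2 m | 20.7 m |
| Available-case with baseline covariate | 38.2 m | 15.1 m |
| Uses M0 and M1, baseline-adjusted | 39.9 m | 14.8 m |
| Uses M0 and M1, not baseline-adjusted | 40.0 m | 20.2 m |

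Baseline adjustment takes the SE from about 21 m to 15 m. Recovering information on missing values adds only 15.1 − 14.8 = 0.3 m to 20.7 − 20.2 = 0.5 m.

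**5. A second mechanism.** Very large simulated arms, SD 99.9 m, baseline/follow-up correlation 0.7, log-odds of drop-out rising by 1 per SD shorter walk.
- At 24% drop-out, an arm mean is too high by about 14 m if drop-out depends on the baseline walk, and by about 20 m if it depends on the follow-up walk itself.
- With 24% in both arms, the bias in the difference is about 0 m.
- With 24% in one arm and 10% in the other, it is about ±8 m (baseline-dependent) or ±11 m (follow-up-dependent).
- Putting baseline in the model reduces these to about 0 m and ±6 m respectively.

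**The case against.** A reader might infer that the stated rule certainly biases the trial, or that it is valid only if missingness is unrelated to health. The documents do not support either reading. They give no reasons for drop-out and no control-arm rate, and health-related drop-out that is the same in both arms leaves the difference essentially unbiased. Nor is the direction fixed. Heavier loss of weak controls understates the exercise effect, and heavier loss of weak exercisers overstates it.

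A reader might also take 24% as a forecast for all 112 patients. It is an external figure used to inflate the PEI group alone.

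The size can fairly be called modest. The 4 m bias is about a fifth of one SE (4/20.7). The illustration in step 3 also favours the remedy, because the 12-week walk is always observed and drop-out depends on nothing else. A model that admits only patients with some follow-up would still leave out those lost before 12 weeks, and no such model fully removes bias from drop-out that depends on unobserved values.

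Finally, imputation details and sensitivity analyses are commonly left to a full analysis plan, so their absence from an article is no fault. All of this stands as a limit on the claim. It does not remove the point, because the article does not leave the method open: it names available-case analysis and unadjusted tests.

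**Conclusion.** The point holds as a risk created by a stated rule. Available-case analysis is fixed while drop-out is expected and four visits are scheduled, and the observed visits are not used to inform the missing ones. Arm means may shift toward fitter patients if drop-out is health-related. The group comparison may be biased, in either direction, only if drop-out or its causes differ between arms. Under the assumptions shown, that bias runs from about 0 m to about 8 m, or about 11 m in the less favourable mechanism, against a true difference of about 40 m. Differential drop-out is an inference from the design and is not stated in the article. The main precision gain from the change belongs to baseline adjustment and should not be credited to the handling of missing data. The change is worth making before the data are analysed.

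**What to change.** - Analyse the 6MWT and the other repeated continuous outcomes by randomised group in one linear mixed model, with M0, M1, M2 and M3 as repeated outcomes and baseline means constrained equal across arms. Patients lost before M1 are then included. An alternative is M1 to M3 as outcomes with baseline as covariate, plus multiple imputation.
- Use multiple imputation for the instrumental-variable and cost/QALY analyses, so that costs and QALYs come from the same patients.
- Keep available-case analysis as a sensitivity analysis. Add a delta-shift analysis for patients who drop out, because the model does not fully remove bias when drop-out depends on unobserved values.
- Report drop-out and its reasons by arm and visit.

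The cost is modest extra analysis work and reliance on a missing-at-random assumption in the main model. The methods are available in SPSS, the package the article names, and no new data are needed.
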